**HISTORY OF PROTOCOL UPDATES**

| Version | Date | Reason for update |
| --- | --- | --- |
| V 1.0 | 17/11/2014 | First version |
| V 1.1 | 01/06/2015 | - Change in contacts Sponsor: Project Manager and Clinical Research Associate - Deletion of Annex 10: the budget table - Addition of two additional investigative centers: - CHR Metz Thionville – Mercy Hospital - Centre de Santé Dentaire (*Center for Dental Health*) - Fondation Sonnenhof à Bischwiller (*Sonnenhof Foundation in Bischwiller*) - Update of the provisonal study schedule. |
| V 2.0 | 15/01/2016 | Substantial amendment (SA1): change in the mode of sterilization |
| V 3.0 | 07/09/2016 | Substantial amendment (SA2):   - Substitution of the investigator at the investigative center CHU of Dijon by [name] [name]   Substantial amendment (SA3):   - Addition of a secondary study objective: operator comfort, which is scored on a numerical scale. |
| V 4.0 | 11/08/2017 | Substantial amendment (SA4):   - Addition of a new investigative center: Centre Hospitalier Emile Durkheim-Epinal (*Emile Durkheim-Epinal Hospital*) and a new principal investigator: [name] [name] - Update in the provisional study schedule: extension of the inclusion period |

**16. List of annexes**

**17. BIBLIOGRAPHIC REFERENCES**

**1.** PROTOCOL SUMMARY

| Title | *OAS: Evaluation of the effectivess and safety of an innovative medical device designed to enhance the oral accessibility of people with a handicap who have behavioral disorders: the Oral Accessibilty Spatula (OAS)* |
| --- | --- |
| Sponsor | *CHR METZ THIONVILLE* |
| Investigator Coordinator | *[name] [name]*  *Department of Odontology*  *CHR METZ-THIONVILLE – Bel Air Hospital*  *[name]*  *[contact] / Email: [contact]* |
| protocol version | *V4.0 produced 11/08/2017* |
| Justification/context | *It is sometimes difficult, even impossible, to access the oral cavity of people with a behavioral handicap. This is because of their defensive reflexes, where they spontaneously limit the amplitude of the mouth opening or keep their mouth open for very short periods only.*    *The currently available means of keeping the oral cavity open are often unsuitable for these patients and alternative devices have not been described in the literature.*  *This problem makes it difficult to perform preventive oral examinations or provide these patients with oral healthcare.* |
| Main Objective | *Evaluation of oral accessibility during the initial oral examination without and then with the oral accessibility spatula (OAS).* |
| Secondary Objectives | *Evaluation of the safety of the OAS*  *Evaluation of the tolerability of the examination without and with the OAS*  *Evaluation of operator comfort when using the OAS* |
| Primary Endpoint | *Visibility and probe-ability of the three tooth sectors (incisors/canines, premolars, and molars) during the examinations without and with the OAS, as indicated by using an Oral Accessibility Score (this score ranges from 0 = no accessibility to 12 = total accessibility)* |
| Secondary Endpoints | *Identification of adverse events and their frequency.*  *Venham Behavioral Rating Scale*  *Numerical scale measuring operator satisfaction* |
| Méthodology / Study design | *Prospective interventional study, multicenter, open-label*  *Only one visit is planned per patient.* |
| Inclusion Critèria | - *Minor or adult patient with an impairment that is accompanied with behavioral difficulties that are already known or are evinced during the oral examination* - *Venham Scale score of 2 or more when the dentist gradually approaches the oral cavity of the person by first touching their hand, then the lips, then attempting to spread the lips)* - *The holders of parental authority over the minor patients, the legal representatives of the minor or adult patients under guardianship, and the adult patients who are under trusteeship and their trustees are informed about the study and then sign an informed consent form* |
| Exclusion Criteria | - *Pregnant or lactating woman* - *Lack of health insurance* - *Patient is under judicial protection but not yet under guardianship* |
| Procédures | *All patients who present with a behavioral disorder, are being consulted for a preventive dental check or oral care, and who satisfy the eligibility criteria (in particular, they have a Venham Scale score of 2 or more* i.e. *they oppose the dentist’s approach to their oral cavity) are included.*  *The oral accessibility of each eligible patient is then rated by using the oral accessibility score (whic ranges from 0/no accessibility to 12/total accessibility), first without the OAS (*i.e. *the standard examination) and then with the OAS.*  *Adverse events and possible injuries are recorded by completing a chart.*  *The Venham Scale is used again to measure the patient’s behavior during the dental examination without and then with the spatula.*  *At the end of the visit, the operator evaluates his/her satisfaction with the OAS by using a numerical scale (the score ranges from 0: unsatisfactory to 10: very satisfactory).* |
| Number of Patients | *When the OAS is not used, 20% of patients have an oral accessibility score of at least 8.*  *The protocol hypothesizes that the OAS will improve this frequency by 20% (*i.e. *40% of the OAS-treated patients will have an oral accessibility score of at least 8). To validate this hypothesis with an α of 5% and a power of 90%, a total of 140 patients is needed. When potential center-related and investigator-related effects and a study drop out rate of 10% are taken into account, the patient number rises to 200.* |
| Duration of Research | *Only one visit is planned per patient.*  *The total duration of the study therefore corresponds to the recruitment period, which is 33 months.*  *Expected start of the study: March 2016*  *End of recruitment: December 2018*  *End of the study: June 2019* |
| statistical analysis | *The principal analysis will be comparison of the oral accessibility scores during the examination with and without the OAS. Each subject will serve as their own control and the examinations will always be conducted first without the OAS and then with the OAS by the same dental surgeon* |
| Expected results | *The expected result is that the OAS will provide a better quality oral examination without risk to the patient. It is expected that dentists will then be provided with the OAS to improve the therapeutic indications for the use of this tool and the quality of interventions. Thereafter, the OAS will be provided to parents, carers, and nursing staff to facilitate preventive oral healthcare in people with disabilities or dependency.*  ***The expected benefits are therefore as follows:***   - *early detection of oral diseases* - *increased effectiveness of the care provided* - *reduction of the indications for care under general anesthesia* - *facilitating toothbrushing, thereby significantly improving the oral hygiene of these people* - *increasing the prevention of oral diseases by making this spatula available to parents, carers, companions, and healthcare professionals.* |

**List of abbreviations**

| ANSM | Agence Nationale de Sécurité du Médicament et des Produits de Santé (*National Agency for the Safety of Medications and health-related products*) |
| --- | --- |
| CHR | Regional Hospital |
| CHU | University Hospital |
| CNIL | Commission Nationale de l’Informatique et des Libertés (*National Commision for Data Protection and Liberties*) |
| CRA | Clinical Research Associate |
| GCP | Good Clinical Practices |
| ICH | International Conference on Harmonization |
| OAS | Oral Accessibility Spatula |
| SAE | Serious Adverse Event |
| SUSAR | Suspected Unexpected Serious Adverse Reaction |

**2. sCIENTIFIC Justification AND GENERAL DESCRIPTION OF THE RESEARCH**

**2.1. name and description of the experimental medical device**

The present research focuses on an oral accessibility spatula denoted as "OAS".

A device for facilitating oral accessibility can be defined by the following criteria:

- effectively helps to open the mouth
- easy to use
- helps the healthcare team to maintain distance from the mouth opening
- aids oral examinations, and possibly toothbrushing and dental care.

The OAS is an **innovative** medical device that aids access to the oral cavity.

The overall objective is the creation of a tool that facilitates oral accessibility in people with a handicap or dependency whose self-protective reactions make it difficult for the dentist to access the mouth during oral examination. This tool is specifically designed for people with behavioral difficulties due to their impairment.

The OAS meets the following criteria:

- shape adapted for the oral cavity of both adults and children
- non-traumatic for the dental structures
- non-traumatic for the mucosal tissues
- easy to use
- good grip
- hygienic, can be cleaned, can be sterilized according to hospital standards (one single sterilization before use, the spatula is intended for single use only)

It is a device that provides technical aid during preventive or curative management. It is not a therapeutic device.

Moreover, this device is not suitable for people who present with a pathological limitation in mouth opening.

**2.2. Summary of the results of available non-clinical and clinical trials that relate to the present research**

There is currently no medical device of this type.

This spatula is novel in that it allows access to the oral cavity and then holds the mouth open during the examination.

This device is more suitable than the classical intraoral mouth gags, which are more difficult to insert into the mouth and keep between the dental arches during the examination.

The current devices that are used to aid oral accessibility are:

- metal mouth gags
- Intraoral rubber mouth props
- spinning top-shaped devices

None of these devices satisfactorily meet the criteria for oral accessibility.

Because of its innovative nature, the OAS has been the subject of a patent application file dated 29/03/2010. The patent was issued on 08/11/2013.

**2.3. Summary of the anticipated and known benefits for and risks to the people participating in the study**

**Benefits for the patient:**

- better accessibility to the oral cavity
- patient can be screened for carious and peridontal lesions
- possible pain from proven lesions can be managed
- the patient’s level of oral hygiene can be assessed
- diagnosis of oral diseases
- a treatment plan that is adapted to the nature of the impairment and the degree of cooperation can be established

**Adverse effects:**

- possible oral lesions (see section 4.4.2).
- inhalation or ingestion of a tooth or tooth fragment
- there are no other study-related risks for people included in the protocol.

The safety of the device will be evaluated during the study

**2.4. Description and justification of the terms of use and the duration of treatment**

The oral management of people with a behavioral impairment is complicated by their instinctive self-protective reactions.

The oral cavity is a unique area in that it is both the aerodigestive junction (where both alimentation and respiration start) and the seat of oral expression.

The self-protective behavior involves withdrawal with forward bending of the head and closure of the mouth.

The advantage of the OAS is that it overcomes the self-protective mouth closure since it can be efficiently inserted into the mouth, thereby facilitating the opening of the mouth.

The duration of treatment is not addressed because the effectiveness of the device will be evaluated during a simple oral examination.

**2.5. Statement that the research will be conducted in accordance with the protocol, GCP, and current regulations and legislation**

The research will be conducted according to the protocol, Good Clinical Practice, and the current regulations.

**2.6. Description of the study population**

The study population consists of adult and/or minor patients who present with a behavioral disorder and who are:

- referred to the Department of Odontology for a preventive assessment or oral healthcare (whatever it may be)
- are cared for as part of an annual oral screening visit within the specialized institution on which the patient depends

The study population therefore consists of people who have a particularly protected status in terms of biomedical research (Articles L1121-8 and L1121-7 of the Code de la Santé Publique [*French Public Health Code*]). In other words, the adult patients are subject to a legal protection order as well as the minor patients.

**3. research Objectives**

**3.1. Primary Objective**

The primary objective of our study is the evaluation of oral accessbility during an initial oral examination, without and then with the OAS.

**3.2. Secondary objectives**

The secondary objectives are:

- Assessment of the safety of the spatula
- Assessment of the tolerability of the spatula, without and then with the spatula.
- Assessment of the comfort of the operator

**3.3. Objectives of any possible ancillary study**

**Not applicable**

**4. Research design**

**4.1. assessment methods**

- *Primary assessment method*

The primary assessment is the visibility and probe-ability of the incisor/canine, premolar, and molar tooth sectors. This assessment is made during a vestibular and palatal/lingua approach.

The visibility and probe-ability are scored so that an "oral accessibility score" that ranges between 0 (no accessibility) and 12 (total accessibility) can be calculated. How this score is calculated is described in section 4.4.1.

- *Secondary assessment methods*

The safety of the spatula will be evaluated by recording the adverse events and determining their frequencies.

The tolerability of the examination, without and then with the OAS, will be evaluated by using the validated Venham Behavioral Rating Scale.

The comfort of the operator during the use of the OAS spatula will be evaluated at the end of each visit by the operator using the OAS, by applying a numerical satisfaction scale whose scores range from 0 (unsatisfactory) to 10 (very satisfactory).

## 4.2. research méthodology

The patients will be recuited:

- either in the Department of Odontology, as part of a preventive assessment or for oral healthcare (whatever it may be)
- or in the specialized institution on which the patient depends, as part of annual oral screening.

For all patients, the assessment will be conducted in one visit.

The study population consists of people who have a particularly protected status in terms of biomedical research. In other words, the adult patients are subject to a legal protection order as well as the minor patients.

The patients will therefore receive information from the investigator that is tailored to their ability to understand.

The information will also be given:

- to the holders of parental authority over the minors
- the legal representatives of minors and adults under guardianship
- the trustees for adults under trusteeship

The informed consent form will be signed:

- by the holders of parental authority over the minors
- by the legal representatives of the minors and adults under guardianship
- by the trustees of the adults under trusteeship

The personal commitment of the patients themselves will always be sought, **as much as possible**, and their refusal cannot be overruled.

Once the consent form has been signed, the investigator will evaluate whether the patient meets the inclusion criteria: the Venhman Scale score will be calculated during a gradual approach to the oral cavity of the person (first touching the hand, then the lips, then attempting to spread the lips). The patient is included if the Venham score is 2 or above, meaning there is opposition to the examination.

If the patient meets all the inclusion criteria and does not meet any of the exclusion criteria, the investigator will proceed to the first examination of the oral cavity **without** the OAS.

He/she will measure the oral accessibility scores and any problems (see section 4.4)

He/she will also calculate the Venham Scale score during the examination without the OAS (evaluation of patient tolerance).

In a second step, the investigator will examine the oral cavity **with** the OAS.

He/she will measure the oral accessibility scores and any problems (see section 4.4)

He/she will also calculate the Venham Scale score during the examination with the OAS (evaluation of patient tolerance).

Finally, after performing both examinations (without and then with the OAS), the operator will evaluate his/her level of comfort when using the OAS spatula compared to the usual examination without the OAS.

## 4.3. Description of the measures taken to reduce and avoid bias

Each patient will their own control.

The examinations will always be done first with the OAS and then with the OAS because it is not desirable to perform an examination that starts with the use of a constraining device. The examination without and then with the OAS will be performed by the same dental surgeon to maximize patient comfort (because inflicting two different operators on the patient could be disturbing and changing operators could prolong the examination).

This design makes it possible to neutralize the operator effect, but it can introduce possible evaluation bias because the same dental surgeon makes the two 2 assessments. However, the only design that would address this bias would be a parallel-arm trial where one arm is examined with the OAS only (*i.e.* there is no initial approach without the OAS). This is undesirable for the patient. To minimize this bias as much as possible, oral accessibility will be assessed with an objective score that involves counting the visible areas of the oral cavity (see 4.4.1). In addition, all investigators will be made aware of the importance of strictly adhering to this score to avoid evaluation bias.

The examination with the OAS will always follow an examination without the OAS, which runs the risk of habituation bias. However, this bias cannot be limited because an examination of the oral cavity must never start with the use of the OAS

To avoid any conflict of interest, we specify that the coordinating investigator of this study, who is also the inventor of the OAS, can be an inclusion operator but cannot perform examinations of the oral cavity to measure oral accessibility.

This study will be conducted as an open-label study because the nature of the study device means that neither the patient nor the investigator can be blinded.

## 4.4. the medical device being studied

## 4.4.1 oral accessibility score variables

The following variables will be evaluated without and then with the OAS (note that a "tooth sector" refers to the indicated teeth on both themaxilla and the mandible):

- intraoral visibility of the left and right incisor/canine tooth sectors
- intraoral visibility of the left and right premolar tooth sectors
- intraoral visibility of the left and right molar tooth sectors
- probe-ability of the left and right incisor/canine tooth sectors
- probe-ability of the left and right premolar tooth sectors
- probe-ability of the left and right molar tooth sectors

Each item is scored from 0 to 2, where:

- 0 = negative result for both the left and right sides of a specific tooth sector
- 1 = positive result for either the left or right side (but not both) of a specific tooth sector
- 2 = positive result for both the left and right sides of a specific tooth sector

The oral accessibility score during the examination without the OAS will be scored from 0 to 12.

The oral accessibility score during the examination with the OAS will be scored from 0 to 12.

## variables for assessing OAS-related adverse events

11 items are used to evaluate the safety of the OAS. These adverse events are described as often occurring when intraoral mouth props, metal mouth gags, and spinning top-shaped devices are used:

- labial injuries
- gingival injuries
- cheek injuries
- lingual injuries
- dental fracture
- dental luxation
- dental expulsion
- nausea/vomiting
- pain
- joint complications
- others

Each item with be scored 1 (yes) or 0 (no).

## 4.5. Expected duration of study subject participation and description of the chronology and duration of all study periods

Duration which which each patient will participate: 1 visit (approximately 30 minutes)

Duration of patient recruitment: 33 months

Total duration of the research: 39 months

Total forecast duration of the research (duration of both inclusion and participation): 39 months

The patient only participates in one visit:

- signing of consent by the patients’ representative if they are a minor or adult under guardianship, by the patients themselves if they are adults under trusteeship

- verification of the eligibility criteria

Examination of the oral cavity **without** the OAS:

- evaluation of accessibility and possible adverse events (see section 4.4)

- score obtained with the Venham Scale during the examination without the OAS.

Examination of the oral cavity **with** the OAS:

- evaluation of accessibility and possible adverse events (see section 4.4)

- score obtained with the Venham Scale during the examination with the OAS.

The operator finishes each visit by using a numerical scale to evaluate how comfortable the OAS spatula was to use.

There is no study-specific follow-up at the end of this visit.

**4.6. Measures to maintain or lift blinding, if appropriate.**

Not applicable, the study is an open-blind study

**4.7. Identification of all data that will be collected directly in case report forms, which will be considered to be source data.**

Not applicable

**4.8. biological sample collection**

Not applicable

**5. Sélection and exclusion of study subjects**

The study population consists of people who have a particularly protected status in terms of biomedical research. In other words, the adult patients are subject to a legal protection order as well as the minor patients.

Research on these populations is justified because:

- it responds to the health needs and priorities of these populations

- the results of the research will be beneficial for these populations

- the study cannot be conducted on another population

- the risks and disadvantages are minor in terms of the expected benefits.

In addition, it is necessary to test the effectiveness and safety of the spatula on minors to confirm that the OAS is suitable for small oral cavities.

**5.1. Inclusion criteria**

- Minor or adult patient with am impairment accompanied with behavioral difficulties (known beforehand or discovered during oral examination)
- Score of 2 or more on the Venham Scale on a gradual approach to the oral cavity of the person (defined as touching the hand, then the lips, then attempting to spread the lips)
- The study-specific informed consent form is signed after the holders of parental authority over minor patients, the legal representatives of the minors and adults under guardianship, and the adult patients under trusteeship and their trustees are given information specific to the study

**5.2. exCluSion criteria**

- Pregnant or lactating woman
- Lack of health insurance
- Patient is under judicial protection but not yet under guardianship

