**5.3. Procédure for premature STopping of the study or exclusion (stopping treatment + stopping follow-up)**

**5.3.1. Criteria and procedures for stopping treatment/medical device use and exclusion**

- *Premature stop criteria*

It is impossible to perform the evaluations, without and then with the spatula, due to patient behavior that involves their physical integrity (score of 5 on the Venham Scale).

- *Follow-up Methods for persons excluded from the study*

Patients with a score of 5 on the Venham Scale will be examined outside the study by using the following medical techniques:

- sedated by inhalation of an equimolar mixture of oxygen and nitrous oxide
- under sedation using Midazolam (intra-rectal or intravenous)
- Under general anesthesia if necessary.

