## Annex 4: operating instructions for the OAS – version N°2 of 15/01/2016

Spatula OAS

Operating instructions

1. **Description and technical characteristics.**

The OAS Spatula is a medical device that helps to attain oral accessibility. It facilitates access to the oral cavity in people who do not have the capacity to provide oral access spontaneously. It is particularly adapted to people with an impairment or dependency in whom access to the mouth is made difficult by behaviors related to their impairment or dependency.

The OAS Spatula is composed of a handle and a blade that is inserted into the mouth. The handle and the blade are interconnected by an intermediate portion that is angled to facilitate the introduction of the blade into the mouth.

- The handle is covered with retention striations that allow a good grip
- The intermediate part bears a depression that will be covered by the thumb
- The blade has a foam-like shape that is rounded at its end and bears symmetrical notches on its edges that allow the blade to wedge between the arches; this prevents slippage of the spatula inside the oral cavity.

The OAS spatula is manufactured by plastics technology. It is made from Polypropylene for medical use, which has mechanical properties that are compatible with the masticatory forces involved on the one hand and with the nature of the dental elements in contact with the OAS spatula on the other hand (it is strong enough not to break and flexible enough not to damage the hard tissue).

1. **Indications.**

The OAS Spatula is indicated in cases of oral accessibility difficulties that relate to the behavioral disorders of the person.

1. **Contraindications.**

The OAS Spatula is not indicated in cases of pathological limitation of mouth opening.

1. **Precautions for use.**

Like any restraining device, the OAS Spatula must be used with respect for the person. In particular, it must be used without applying any physical force that could traumatize the person on a physical and/or emotional level.

1. **Adverse reactions.**

The use of the OAS Spatula may potentially associate with several traumatic injuries.

These are essentially the risks of:

- mucous injuries (labial, gingival, cheek, …)
- lingual injuries
- dental fracture
- dental luxation
- dental expulsion
- nauea and vomiting
- pain
- joint complications
- inhalationor ou ingestion of dental fragments

1. **Instructions for use.**

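### The protocol calls the spatula unsuitable for people with pathologically limited mouth opening, but its eligibility criteria and procedure never screen for that condition

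*Protocol*

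**What the plan says.** Two places in the protocol limit who the spatula is for. Section 2.1 ends its description of the device with the statement that "this device is not suitable for people who present with a pathological limitation in mouth opening". Annex 4, under its contraindications heading, says "The OAS Spatula is not indicated in cases of pathological limitation of mouth opening".

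Eligibility is set elsewhere. Section 5.1 asks for three things: an "impairment accompanied with behavioral difficulties (known beforehand or discovered during oral examination"), a Venham score of 2 or more on a gradual approach to the mouth, and signed consent. Section 5.2 excludes on three grounds: "Pregnant or lactating woman", "Lack of health insurance" and "Patient is under judicial protection but not yet under guardianship". The protocol summary gives the same two lists.

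Section 4.2 then describes the visit. If the patient satisfies section 5.1 and "does not meet any of the exclusion criteria, the investigator will proceed to the first examination of the oral cavity". That first look is unaided, and the examination with the spatula follows as a second step. The only premature stop criterion, in section 5.3.1, is that the evaluations cannot be done "due to patient behavior that involves their physical integrity (score of 5 on the Venham Scale").

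**The concern.** The people whom section 2.1 and Annex 4 set aside are not the people whom section 5 keeps out. A behavioural difficulty does not rule out a coexisting physical limitation of opening, so a patient can satisfy every criterion in section 5 and still fall under the device's contraindication.

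Two things are at stake. The first is safety. Joint complications, dental fracture, dental luxation and pain are on the list of expected events in section 8.3.3. Participants are minors and legally protected adults, and section 5 justifies studying them partly because the risks are minor relative to the benefits. The second is the analysed population. Whether such a patient contributes a with-spatula score depends on which part of the protocol the operator acts on, and nothing in the protocol settles it.

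**Working it through.** No calculation applies to the core point. The check is to follow one hypothetical patient, with a behavioural disorder and a pathologically limited mouth opening, through the text.

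1. **Device suitability (section 2.1, Annex 4).** The limitation is named in both places. Both set the patient aside.
2. **Inclusion (section 5.1, summary).** There are three criteria: impairment with behavioural difficulties, Venham 2 or more, and consent. None refers to how far the mouth can open, so the patient can meet all three.
3. **Exclusion (section 5.2, summary).** There are three criteria: pregnancy or lactation, no health insurance, and judicial protection without guardianship. The limitation appears in 0 of the 3, in both lists.
4. **Procedure (sections 4.2 and 4.5).** After the eligibility check come the examination without the spatula and then the examination with it. No check of mouth opening is described before or between them. The first examination may reveal a limitation, but no instruction says what follows.
5. **Stopping (section 5.3.1).** The single criterion is behavioural (Venham 5). A limitation of opening does not trigger it.

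From here two routes are open.

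- **Route A: the operator follows sections 5 and 4.2.** The spatula is used in a patient for whom section 2.1 and Annex 4 say it is not suitable or not indicated. That patient's scores and adverse events enter the results.
- **Route B: the operator follows Annex 4 and withholds the spatula.** The patient has been consented and enrolled but has no with-spatula score. Sections 9.5 and 9.7 remove subjects with incomplete data from the comparison of accessibility scores. If counted as a drop-out, the patient is not replaced (section 5.3.3).

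One further comparison suggests an oversight. Annex 4 also notes that the spatula has not been tested in pregnancy or lactation, and section 5.2 carries a matching exclusion. The one condition that Annex 4 lists as a contraindication has no counterpart in section 5, and no passage explains the difference.

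**The case against.** **Annex 4 is itself a safeguard.** It is part of the protocol. Section 6.1 says the instructions were written to standardise technique, the users are dental surgeons accustomed to working in the mouth, and under section 12 the investigators commit to following the protocol in full. An operator may well withhold the spatula. This stands in part: it would be wrong to say that every such patient would be examined with the device. It does not remove the conflict, because withholding leads to Route B, for which the protocol has no rule.

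**The case report form and the investigator brochure are not shown.** Mouth opening may be screened there. That is possible, but it would not align section 5.2 with section 2.1.

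**The effectiveness result would be biased.** A reader might infer that these patients dilute the measured gain. The documents do not support a figure. They give no frequency, and section 9.2 states its 20% and 40% for the patients in general, so those figures may already include such people. Suppose, purely as an assumption, that 10% were affected and none reached a score of 8 by either method. The planned gain would fall from 20 to 20 × 0.90 = 18 points. With independent paired responses, the discordant proportions would be 0.9 × 0.40 × 0.80 = 0.288 and 0.9 × 0.20 × 0.60 = 0.108. The McNemar test at N = 140 would then have z = (√140 × 0.18 − 1.96 × √0.396) / √(0.396 − 0.18²) = (2.130 − 1.233) / 0.603 = 1.49, a power of about 93%, still above the planned 90%. Any such dilution would run against the device, and under Route B it would not arise at all.

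**The risk could be painted more darkly.** A reader might infer that the spatula forces the mouth open, or that these patients cannot report pain. Section 6.1 does speak of enough force to open the mouth, but Annex 4 warns against traumatising force and asks for gentle rotation. The Venham description at score 2, which is eligible, is of a patient who answers questions and protests verbally. Neither statement can be made generally.

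**Conclusion.** The point holds as an internal contradiction that bears on safety. The limitation is named in two places as a reason not to use the device. It appears in none of the three exclusion criteria, none of the three inclusion criteria, no step of the procedure and not in the stop criterion. An investigator who applies sections 5 and 4.2 exactly can be led to use the device against its own instructions; one who applies Annex 4 is left with an enrolled patient and no rule.

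The conclusion rests on the protocol text alone and on one modest premise, that a behavioural disorder and a physical limitation of opening can coexist. It does not assert that any such patient was or will be examined with the spatula, nor how many there might be. With no frequency in the documents, no effect on the estimate or on power is claimed. The grounds are participant safety and a uniformly defined analysed population.

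**What to change.** The sponsor should reconcile the summary and sections 4.2, 5.1 and 5.2 with section 2.1 and Annex 4, so that all of them identify the same ineligible patients. Which wording prevails is a clinical decision for the sponsor and investigators. The agreed wording should then be carried to the eligibility check made at the visit, and patients already included should be reviewed against it, with any affected cases reported.

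The drafting is short, but the change is probably not a minor one. Section 12.3 gives a modified inclusion criterion as an example of a substantial amendment, which needs a favourable opinion and authorisation before it is put into effect. A changed exclusion criterion would plausibly be treated the same way. The review of patients already included adds some work at the sites.
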